### Cardiorespiratory fitness

Cardiorespiratory fitness was measured with an intermittent practicable running field test (the Andersen-test [22]) that has demonstrated reliability and validity for our target age group [23]. The Andersen-test was administered as per standard procedures. The children were tested indoors on a wooden or rubber floor in groups of 10–20 children. The test required 10 min to perform. Children ran from one end line to another (20 m apart) in an intermittent to-and-fro movement, with 15-s work periods and 15-s breaks (standing still). We recorded the distance covered as the outcome for analysis.

### Muscle strength

Muscle strength (i.e., endurance, isometric and explosive strength) was measured using reliable and validated selected tests from the Eurofit test battery [24]: **1)** Upper limb strength – handgrip strength using a hand dynamometer (Baseline® Hydraulic Hand Dynamometer, Elmsford, NY, USA); 2**)** Explosive strength in the lower body, standing broad jump. Muscle strength tests were recorded both individually and as a composite score for analyses.

### Motor skills

Motor skills were measured using a battery of three tests: **1)** Catching with one hand and throwing at a wall target constitute the aiming and catching subgroup of the movement-ABC-2; **2)** Throwing at a wall target; **3)** Ten times 5 m sprint. Tests **1)** and **2)** are from the Movement Assessment Battery for Children 2 (Movement ABC-2), age band 3 (11–16 years) [25], and test **3)** is from Eurofit test battery [24]. Reliability and validity of these tests are well documented [26–29]. The Movement ABC-2 demonstrated good concurrent and convergent validity [30, 31]. We recorded motor skills tests both individually and as a composite score for analyses.

### Anthropometry and maturity

Body mass (weight; 0.1 kg) was measured using an electronic scale (Seca 899, SECA GmbH, Hamburg, Germany) with children wearing light clothing. Stature (height; 0.1 cm) was measured with a portable Seca 217 (SECA GmbH, Hamburg, Germany). The child was asked to face forward, with shoes removed. We calculated body mass index (kg · m^−2^) as weight (kg) divided by the height squared (m^2^).

Waist circumference was measured with a Seca 201 (SECA GmbH, Hamburg, Germany) ergonomic circumference measuring tape. The measure was taken two cm over the level of the umbilicus (0.5 cm) with the child’s abdomen relaxed at the end of a gentle expiration. The child stood with arms hanging slightly away from the body. We collected two measurements from each child. If the difference between measures was a greater than one cm, we obtained a third measurement; the mean of two closest measurements are used for analyses.

Body fat was measured using four skinfold thickness sites (biceps, triceps, subscapular, and suprailiac) on the left side of the body using a Harpenden skinfold caliper (Bull; British Indicators Ltd., West Sussex, England) as per the criteria described by Lohmann et al. [32]. The Harpenden skinfold caliper has been tested for validity and reliability in children [33]. All measurements were conducted in a private room. The caliper was placed around the skinfold one cm below and to the left where the skin was held between thumb and forefinger. We collected two measurements at each site (in sequence). If the difference between measures was a greater than two mm, we obtained a third measurement; the mean of the two closest measurements are used for analyses. The skinfold calipers was calibrated each time they were moved between measurement sites.

Children self-assessed their pubertal stage as per the Tanner method [34] using a scale of color images proposed by Carel and Leger [35]. Children were given standardized series of images with explanatory text. We used a scale based on pictures of pubic hair for both sexes and of breast and genital development for girls and boys, respectively. We created a relaxed atmosphere for this assessment and the researcher was of the same sex as the child. In a private room, children were asked to read the brief descriptions for each stage, and instructed to put a checkmark in the box below the picture that best represented their stage of development for each component.

### Blood pressure

Systolic and diastolic blood pressure (BP) was measured using the Omron HBP-1300 automated BP monitor (Omron Healthcare, Inc, Vernon Hills, IL, US). The device is validated as per the AAMI protocol using the ANSI/AAMI/ISO standard (Omron, 2015) [36]. Children rested quietly for ten minutes in a sitting position with no distractions before BP was measured. During measurement, each child sat in a quiet room; BP was measured on the upper right arm using an appropriate sized cuff. We took four measurements, with a one-minute interval. We used the mean of the last three measurements for analyses. If a difference > five mmHg between measurements was found, we obtained one extra measurement, in which case the mean of the last four are used.

### Blood samples (factors impacting risk of metabolic disease)

After an overnight fast, between 08:00 a.m. and 10:00 a.m., a nurse or phlebotomist collected an intravenous blood sample from each child’s antecubital vein. Serum was obtained according to a standardized protocol consisting of the following steps: 1) Blood plasma was collected in 5 ml tubes with gel (Vakuette® Serum Gel with activator, G456073). 2) Tubes were carefully turned upside-down five times and placed vertically for coagulation. 3) After 30 minutes the sample was centrifuged at 2000 G for 10 minutes. Serum was then visually inspected for residues and centrifugation was repeated if residue was present. 4) The serum tube was kept in refrigerator at 4 °C before pipetting 0,5 ml into cryo tubes. 5) The cryo tubes were then stored at -80 °C prior to biochemistry analyses. 

Serum samples were analyzed for constituents related to traditional risk factors for NCDs, such as insulin, glucose and the standard lipid panel (triglycerides, total cholesterol, high density lipoprotein cholesterol (HDL) and low density lipoprotein cholesterol (LDL)) using standard laboratory methods. Baseline and post intervention samples were analyzed at the same time in one batch at an ISO certificated laboratory.

Analyses of low molecular weight metabolites and lipoprotein distribution was performed for serum samples using proton nuclear magnetic resonance (1H-NMR) spectroscopy. The proton NMR profiles of low molecular metabolites (fatty acids and amino acids) were obtained by using a standard experimental set-up [37]. For lipoproteins we made a minor modification to the experimental protocol used by Mihaleva et. a.l (2014) [38]. Lipoprotein features such as subclass concentrations for HDL, LDL etc. and average particle size of each main class were derived from the NMR profiles. Fatty acid analysis was performed according to the following protocol: 200 µL serum sample is weighed into 10 mL glass tubes and water evaporated under nitrogen, followed by adding 150 µL internal standard (triheptadecanoin, 0.4855 mg/mL). After evaporating the solvent the samples are derivatized to fatty acid methyl esters (FAME) by direct esterification in methanolic HCl at 90 °C for 2 h under nitrogen atmosphere [39]. FAMEs will be extracted and analyzed by gas chromatography as described in Gudbrandsen et al. [40]. The samples are run in a randomized sequence and the FAME reference mixture GLC-461 (Nu-Chek Prep, Elysian, MN, USA) will be analyzed as every 10th sample. Chromatographic areas are corrected by empirical response factors calculated from the GLC-461 mixture. The amounts of FAs are thereafter quantified by means of the internal standard. The total amounts of FAs in each serum sample are converted to amounts in μg per g sample by dividing with the sample weights. 

### Questionnaires: children, parents/guardians, teachers

#### Children

Mode of transport to school, levels of leisure time physical activity, sedentary behavior and psycho-social and environmental correlates of physical activity were assessed with a questionnaire developed for youths also used in a large national representative surveillance study of physical activity among Norwegian children and youth [41, 42].

Children’s QoL was assessed by self-report using the Kidscreen-27 questionnaire [43], which consists of 27 items covering the following five QoL dimensions: **1**) physical well-being (5 items); **2**) psychological well-being (7 items); **3**) parents/guardians relations & autonomy (7 items) **4**) social support & peers (4 items); and **5**) school environment (5 items). The Kidscreen-27 questionnaire was developed simultaneously in several European countries, and has been validated in Norwegian children aged 10 [44] and 8–18 [45] In order to assess well-being at school and predictors for this, we also used the teacher and classmate support scale [46].

Physical activity preferences were assessed with a questionnaire created by the ASK group. The children rated their preferences for each of 28 different activities on a scale from one to ten.

#### Parents/guardians

We obtained self-reported height and weight from parents/guardians. We assessed physical activity habits, physical activity in leisure time and everyday living with a questionnaire developed for adults [42]. This questionnaire also assessed background variables (ethnic background, income, education and job description), as well as psychological, social and environmental determinants of physical activity.

#### Teachers

To assess behavioral self-regulation of children from I-schools, we used 10 items from the Child Behavior Rating Scale (CBRS) [47]. The original CBRS was designed to evaluate a child’s task behavior and social behavior with peers and adults [48]. More recent studies have identified a 10-item factor that describes child behavioral self-regulation in a classroom setting [49]. Teachers were asked to rate children’s practical behavior on a five point Likert scale ranging from 1 (never) to 5 (always) to indicate how frequently a given behavior occurs. The CBRS is a reliable and valid tool that has been used in multiple studies in Western countries [50, 51]. After the intervention period, the teachers from the I-schools were asked to provide a self-report survey evaluation of the ASK intervention.

### Qualitative study of embodied experiences and pedagogical processes

We investigated the embodied experiences and interpersonal relationships of teaching and learning in physical activity from the perspectives of children, teachers and parents/guardians using qualitative methodologies. The purpose was to obtain an in-depth understanding of pedagogical processes taking place in the ASK study. More specifically, we identified purposive sample of classes from two I-schools and two C-schools. The sample criteria emphasized variation in school location, school and class size, teachers’ education and experience with PE and physical activity, and the schools’ overall focus on physical activity. In total 100 children with parents’/guardians’ approval and seven teachers provided informed written consent to participate. All children participated in a drawing and writing task and one group interview. The students were also observed by the researcher during one PE lesson. This data, together with teachers’ description of their students in PE lessons, were used to choose children to further in-depth studies.

We conducted in-depth interviews and field observations including short video recordings with 32 children. Teachers were interviewed (individually and in groups) and observed; we also interviewed two groups of parents. We deem insight attained using multiple methods and perspectives to be essential in research with children, as adult researchers may have difficulty interpreting a child’s perspective [52, 53]. Further, a deeper understanding of childrens’, teachers’, and parents’/guardians’ perspectives enriched and gave a nuanced picture of processes leading to certain outcomes from the main trail. Data (i.e., transcripts of interviews, field notes, drawings and writings, pictures and video recordings) were structured and explored using the software program Nvivo 10 (QSR International Pty Ltd 2015). Developing in-depth knowledge is an iterative process where preliminary interpretations of the empirical material are brought together with discussions on theoretical significance in increasing detail.

We consider empirical data as a construct created in a specific cultural and historical context, influenced by the interplay between the researcher and the participant, and the researcher’s theoretical underpinning. Empirical data are used as “a critical dialogue partner” and as an inspiration to challenge and rethink established taken-for-granted assumptions and theories [54]. Thus our approach differed from a more conventional approach where empirical data are seen as separate from theory, but are used to guide and validate theory development. By these means we aim to interpret the children’s embodied experiences and pedagogical practices during the ASK intervention as an interactive whole where researchers’ pre-understanding, alternative theoretical input, and empirical data constitute the dialogue setting [54].

We further created a reflexive account on children’s embodied experiences and pedagogical practices during the ASK intervention. Thus, the qualitative approach thus shed light on «what’s going on» in schools during the intervention period: How do children interact with each other and the teachers within the schools during the intervention, and, in particular, how is it to be a child in an I-school? In addition, this gives us a basis to discuss the teaching and learning processes, the possible benefits and pitfalls in the intervention, as well as to evaluate whether the intervention and the ASK study as a whole might serve as tools towards creating an improved atmosphere for learning in the schools in the future.

### E. Adherence

Regarding adherence to the intervention program, school administrators at the 57 schools recorded every child’s absence from school. Administrators also recorded children’s injuries and the names of children who did not participate in physical activity lessons.

We assessed the extent to which the intervention was implemented (dose), the quality of the implementation (fidelity), as well as feasibility as perceived by teachers and others.

ASK teachers at the 28 I-schools completed a report each week that described activities performed throughout the school day, the intensity of the activities (on a 1 to 3 scale) and the number of minutes allocated to physical activity/PE in each ASK session. All 29 C-schools, at the end of the school year, completed a report that describes the activities that were performed and the estimated time allocated to physical activity/PE during the school year (minutes/week).

### F. Statistical considerations/Statistical methods

#### Randomization procedure

The randomization procedure is explained in section 2a.

#### Blinding

Blinding of children and schools was not possible due to the nature of the experiment. However, only the project management group has formal knowledge of group assignment. The data manager and statisticians are blinded to group allocation until analyses are conducted.

#### Power calculations/Sample size and power

The ASK study was designed to detect an effect size (Cohen’s D) of 0.35 between two groups for change in academic performance. Sample size calculations were performed using standard formulas, given ɑ = 0.05, 1-β = 90 %, group ratio 1:1 and correlation of repeated measurements = 0.7, leading to a naive n = 103 children in each group. Due to the cluster-randomized controlled trial (RCT) design, the sample size was corrected for the design effect using *formula 1;* Design Effect = 1 + [(CV^2^ + 1)*n – 1]* (ICC), where CV = coefficient of variation for n, n = number of children within each cluster, and ICC = intraclass correlation coefficient. Thus, after accounting for school clusters, we required a sample size of 468 children in each arm (INT; CON). This is based on an ICC = 0.15, n = 16.2 after accounting for 20 % attrition at the subject level, and CV = 0.72 (design effect correction factor = 4.54). The assumed ICC is a conservative estimate compared to the expected ICC of 0.03 to 0.07, which lay the foundation for the sample size of the A+ PAAC study [55]. For secondary outcomes we assume an ICC of 0.05 to 0.10 [56]. Accepting the assumptions above, the target sample size allowed us to detect a significant difference between the groups for variables reaching an effect size of 0.24 (ICC = 0.05) to 0.30 (ICC = 0.10) or higher.

#### Plan for analysis

Our main analysis in order to assess the effectiveness of the ASK intervention are based on and intention to treat analysis [57, 58]. We also acknowledge the importance of conducting per-protocol analyses to determine efficacy based on schools that showed fidelity to the model and performed the physical activity intervention as intended [59]. Therefore, we conducted secondary analyses of children who participated in ≥80 % of the physical activity-based intervention and schools which delivered ≥80 % of the physical activity-based intervention as we deem this acceptable adherence to the intervention itself.

We describe missing data using appropriate flow charts [60] that also allowed for investigation of missing data mechanisms and assumptions that underpin statistical analyses. Missing data was imputed from all available relevant variables by means of multiple imputation using a Markov Chain Monte Carlo procedure with 20 iterations, with an assumption that data are missing at random. We performed sensitivity analyses to evaluate the stability of results under various assumptions of missing data.

We used a mixed-effects model to test the between-group difference (intervention vs. control) for the main outcome (academic performance), controlling for baseline values and including school as a random effect. The per-protocol analysis was adjusted for differences between groups as appropriate.

We conducted our analyses using the newest available version of IBM SPSS (IBM SPSS Statistics for Windows, Armonk, NY: IBM Corp., USA). A two-sided p-value ≤ 0.05 were considered statistically significant.

We conducted defined moderator-mediator analyses a priori to evaluate characteristics of children and pathways that could influence the effect of the intervention on academic performance. We identified potential moderators that include both characteristics of the children and baseline values for specific secondary outcomes. We included change in executive function, motor skills, physical activity, physical fitness, adiposity and other risk factors for lifestyle-related non-communicable diseases in mediation-analyses. We used a similar strategy to evaluate moderators and mediators of secondary outcomes. As a part of the investigation of possible moderators of the effects evaluated, we conducted subgroup-analyses defining subgroups by quintiles or quintile split and testing group*subgroup interaction terms. For mediation analyses we used structural equation modeling. We also used multivariate linear regression and exploratory analyses [61, 62] to evaluate associations between secondary outcomes and academic performance, and to explore associations among independent variables.

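### Continuous baseline moderators are tested by quintile-based subgroups; a continuous interaction test would be the better main test if moderation is roughly linear

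*Protocol article*

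**What the plan says.** The moderator strategy is in the Protocol article, section F, Plan for analysis. The candidates are "potential moderators that include both characteristics of the children and baseline values for specific secondary outcomes". The Background names cognitive function, physical fitness, adiposity, motor skills and quality of life as possible mediators or moderators. Section D measures most of these on continuous or many-valued scales, for example distance run, skinfold thickness, waist circumference and test scores.

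The test is introduced with "As a part of the investigation of possible moderators of the effects evaluated" and continues: "subgroup-analyses defining subgroups by quintiles or quintile split and testing group*subgroup interaction terms". The article does not define the second form of grouping, and it does not say whether the interaction test is an omnibus test or a trend test. It gives no reason for cutting the variables. A similar strategy is announced for moderators of secondary outcomes.

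The significance rule is "A two-sided p-value ≤ 0.05 were considered statistically significant". The sample-size section covers between-group effects only: the trial was "designed to detect an effect size (Cohen’s D) of 0.35 between two groups for change in academic performance", with "1-β = 90 %, group ratio 1:1 and correlation of repeated measurements = 0.7". No interaction effect size or interaction power is given.

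**The concern.** An interaction test generally has less power than the main-effect test in the same sample. Replacing a continuous moderator by groups weakens it further in two ways. Differences between children in the same group no longer contribute, and a test over five groups spends four degrees of freedom where a linear term spends one. If the true pattern is a steady gradient, for example more benefit the lower the baseline fitness, both losses apply and little is gained in return.

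At stake is the trial's ability to say which children benefit. The Abstract, the Background and the analysis plan all give moderation as an aim, and the strategy carries over to secondary outcomes, so any loss recurs across many tests.

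**Working it through.** **The plan's own figures.** With d = 0.35, two-sided alpha 0.05, power 90% and correlation 0.7, the SD of change is √(2 × (1 − 0.7)) = 0.775. The naive n is 2 × [0.775 × (1.960 + 1.282) / 0.35]² = 102.9, so 103 per group. The design effect is 1 + [(0.72² + 1) × 16.2 − 1] × 0.15 = 4.54, and 103 × 4.54 = 467.6, so 468 per arm. These match the article, as do the secondary detectable effects of 0.24 and 0.30. None of them concerns an interaction, so the rest is an illustration from a chosen benchmark.

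**Assumptions (not from the article).** Linear moderation; a standard normal moderator; a continuous 1-df interaction test with 80% power at two-sided alpha 0.05.

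**Method.** The 1-df chi-square test reaches 80% power at noncentrality 7.849. Grouping multiplies this by the share of moderator variance that the groups retain. Power is then read from the noncentral chi-square distribution on the matching df (5% critical values: 3.84 on 1 df, 9.49 on 4 df).

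**Share retained.**
- Five quintiles: the group means are ±1.400, ±0.532 and 0. The share is 0.2 × (2 × 1.400² + 2 × 0.532²) = 0.897.
- One cut at the 20th or 80th percentile: the normal density at the cut is 0.280. The share is 0.280² / (0.2 × 0.8) = 0.490.
- Quintile number (−2 to 2) as a linear score: the covariance with the moderator is 0.2 × 2 × (2 × 1.400 + 0.532) = 1.333 and the score variance is 2. The share is 1.333² / 2 = 0.888.

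**Power.**

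| Test | Noncentrality | df | Power |
|---|---|---|---|
| Continuous | 7.849 | 1 | 80.0% |
| Quintile trend score | 7.849 × 0.888 = 6.97 | 1 | 75.2% |
| Five quintiles, omnibus | 7.849 × 0.897 = 7.04 | 4 | 54.3% |
| One 20/80 cut | 7.849 × 0.490 = 3.85 | 1 | 50.0% |

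Top versus bottom quintile alone gives 69.9%.

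**Checks.** Simulation with 936 children (2 × 468), 3000 runs, individual level and no clustering gave 80.5% (continuous), 74.9% (trend), 53.4% (omnibus) and 48.7% (20/80 cut). A uniform moderator gives 57.5% (omnibus) and 49.2% (20/80 cut). Starting from 90%, the omnibus test falls to 68.7% and the 20/80 cut to 62.1%.

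**The reverse case.** Suppose moderation is confined to one outer quintile and the matching 20/80 cut has 80% power. The squared correlation between a normal moderator and that quintile's indicator is the same 0.490. The linear test therefore has noncentrality 3.85 and power 50%. The omnibus quintile test keeps the full 7.849 on 4 df and has about 60%. For a symmetric U-shape, the linear test has essentially no power.

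**The case against.** The strongest objection is that linear moderation is the one shape that most favours a linear test. If only the least fit children gain, a cut at the lowest quintile does better, as the reverse case shows. That pattern is not far-fetched: under Intensity, the article asks teachers to take particular care to include children who are less fit or less keen on activity. This stands. Grouping cannot be said to bring no gain, and a linear term should not be the sole test.

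Three stronger readings are tempting and the document does not support them.

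- A reader might infer that moderation is tested solely after grouping. The sentence presents the subgroups as one part of the moderator work, so a continuous test is not excluded.
- A reader might take 50–54% as the power of this trial's interaction tests. The article claims no interaction power. The 80% start is a benchmark, and the low figures belong to two particular forms of the test. A trend over quintiles, equally compatible with the text, loses only about 5 points.
- A reader might infer that the two forms of grouping leave room to report the more favourable one. The article says the moderator analyses were defined in advance. Which form applies to which moderator is a detail that an analysis plan not shown here may settle.

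**Conclusion.** The point holds as an improvement to secondary analyses. The only moderator test described groups variables that are largely continuous, and no reason is given. With linear moderation, a normal moderator and an 80% continuous test as benchmark, the cost runs from about 5 points (trend over quintiles) to 26 points (omnibus) and 30 points (20/80 cut). No quintile-based form examined beats the continuous test under linear moderation. With moderation confined to an outer quintile the ranking reverses, so the case for a continuous main test depends on pairing it with a check for curvature. The primary comparison of academic performance does not depend on any of this.

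**What to change.** For each continuous moderator, state one main interaction test: group × centred continuous baseline value, in the mixed model with school as a random effect that the plan already uses. Add one curvature check stated in advance, such as a spline interaction with its degrees of freedom fixed, and say how it will be read if it disagrees with the linear test. Keep quintile subgroups to display effect estimates.

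The cost is a change of analysis wording and a rerun on data already collected. The downside is less power for the linear term when moderation is confined to an outer quintile (about 50% where the matching 20/80 cut has 80%) or is U-shaped. The curvature check is there to cover this.
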